## Abstract

**Background:**

Impacted fetal head (IFH) at full dilatation caesarean section (CS) is an increasingly recognised obstetric emergency associated with significant maternal and neonatal morbidity. Despite its importance, there is limited evidence to guide management, particularly the use of disimpaction devices.

**Methods:**

LIFT is a prospective observational trial comparing the use of two commercially available disimpaction devices—the Fetal Pillow^®^ and the Tydeman^®^ Tube —for the management of IFH at full dilatation caesarean section.

**Discussion:**

The LIFT study will compare the performance of the Fetal Pillow^®^ and Tydeman^®^ Tube in the management of IFH and contribute to the development of an evidence base to support best practice. As awareness of the clinical significance and implications of IFH continues to grow, generating robust data on available management options is essential. This study represents an important step toward optimising the safe and effective management of this challenging obstetric emergency.

**Trial registration:**

NCT07372768, registered 28/01/2026, https://clinicaltrials.gov/study/NCT07372768.

## Background

Impacted fetal head (IFH) is a recognised and important complication of emergency caesarean section (CS), especially those performed in advanced labour (7–9 cm) or at full dilatation (10 cm). It occurs when the fetal head is low and wedged in the maternal pelvis, making it challenging for the operator to deliver and ‘requires the use of additional manoeuvres and/or tocolysis to disimpact and deliver the fetal head’ [1]. It is estimated to complicate 10% of all emergency CS and 16–32% of all those a full dilatation [1].

IFH is associated with significant maternal and neonatal morbidity including uterine extensions, haemorrhage, visceral injury, sepsis, and fetal trauma such as skull and long bone fractures, hypoxic ischaemic encephalopathy and perinatal mortality [2]. A recent UK Obstetric Surveillance Survey (UKOSS) demonstrated that 3% of babies suffer severe injury or die secondary to complications of IFH and 6% of mothers require admission to intensive care units [3].

With the serious complications associated with IFH, it follows that there are significant medicolegal consequences. The UK’s National Health Service Resolution’s Early Notification Scheme identified that IFH was a contributory factor in 9% of all cases of severe brain injury, and nearly 10% of all maternity claims [4, 5]. In the UK, maternity accounts £3.5 billion of the notified claims and £1.3 billion of total clinical negligence payments in 2024/25 [6].

There is no consensus amongst clinicians on the best management technique and various have been described, including repositioning the operating Table [7], switching the delivering hand [7], administration of tocolytics [8, 9], and additional manoeuvres including vaginal push-up [10, 11] or reverse breech extraction [12]. Disimpaction devices, such as the Fetal Pillow^®^ and Tydeman^®^ Tube have also been developed [13]. There is no consensus on the optimal management of IFH and selection of manoeuvre or device is currently largely dependent on clinician experience or preference.

Disimpaction devices aim to elevate the fetal head vaginally to aid delivery, and are an alternative to the vaginal push up technique, which has been associated with increased maternal and neonatal morbidity.

The Fetal Pillow^®^ is a medical device designed to disimpact the fetal head at the time of full dilatation CS. It is a silicone balloon device that is inserted vaginally into the posterior fornix beneath the fetal head. It is inflated with up to 180mls of water, aiming to disimpact and elevate the head before starting the CS [14]. Currently it is used in the United Kingdom, the United States of America, New Zealand and Australia [15, 16].

The Tydemanâ Tube is a novel disimpaction and vacuum release device which consists of a semi-rigid wide bore silicone tube and a flexible silicone cup [17]. There are three components to the device: the cup, which is angled to fit against the fetal head and encourage the elevating force to be both superior and anterior in direction, whilst spreading force over a large area to minimise localised pressure; the tube, which serves as a handle and is hollow with a wide internal diameter, and finally the end-piece, which has a marker to ensure correct orientation during use. The device is inserted by an assistant to elevate the head by pushing it upwards, disimpacting the head from the pelvis and facilitating delivery [17]. The wide bore of the tube allows air to enter from below and ameliorate any vacuum effect. The Tydeman^®^ Tube may be inserted into the vagina in late labour from 7 cm dilatation before or during a CS, when an IFH is either anticipated or is encountered unexpectedly [17].

At present there is a paucity of evidence underlying the use of disimpaction devices [18]; therefore, the LIFT study has been developed to compare the Fetal Pillow^®^ and Tydeman^®^ Tube in the management of an IFH.

## Methods

### Aims and objectives

The aim of the LIFT trial is to compare the effectiveness of the Tydeman^®^ Tube and the Fetal Pillow^®^ for the management of an IFH at full dilatation caesarean section. The aim of the substudy is to compare the effectiveness of the Tydeman^®^ Tube with usual care for management of an IFH at CS between 7 and 9 cm dilatation.

The primary objective is to determine whether the Tydeman^®^ Tube is as effective as the Fetal Pillow^®^ for managing an IFH at full dilatation CS, by comparing time from uterine incision to delivery after using the devices.

The secondary objectives are:

to compare maternal and neonatal outcomes following the use of the Tydeman^®^ Tube or Fetal Pillow^®^ in the main study, and between the Tydeman^®^ Tube and control group in the substudyto evaluate the acceptability of both devices to women and clinicians

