### Design

This is a prospective non-inferiority observational comparison trial with two sequential interventional arms, the first using the Fetal Pillow^®^ and the second using the Tydeman^®^ Tube. Each device has regulatory approval for routine use and therefore can be introduced into clinical practice.

At trial commencement, obstetric and midwifery staff will be trained to use the Fetal Pillow^®^ by members of the research team during dedicated training sessions. The Fetal Pillow^®^ will then be introduced into clinical practice for 3–6 months for use during all full dilatation CS, or until the recruitment target is reached (*n* = 30). The Fetal Pillow^®^ will be inserted and inflated prior to full dilatation CS, in all eligible women. Consent will be sought retrospectively, see ‘Patient Recruitment’. Once the recruitment target for the Fetal Pillow^®^ has been reached, the device will be withdrawn from clinical areas and will no longer be available for use.

Obstetric and midwifery staff will then be trained to use the Tydeman^®^ Tube and the above process repeated over a 3–6-month period, or until the recruitment target is reached (*n* = 30). For eligible women, the Tydeman^®^ Tube will be inserted prior to commencement of all full dilatation CS and will be used to elevate the fetal head if felt to be required during the caesarean by the operating surgeon.

Should recruitment be reached in a shorter time frame than expected then each arm will continue for the set time frame (3–6 months) to allow for increased data collection and loss to follow up, to a maximum of 40 women per arm.

During the Tydeman^®^ Tube arm of the study, additional Tydeman^®^ Tubes will be available for clinicians to use at their discretion for caesarean sections performed at 7–9 cm cervical dilatation as per the manufacturer’s Instructions for use, which stipulates that the Tydeman^®^ Tube can be used from 7 to 10 cm. If, during a caesarean section, the operating surgeon unexpectedly encounters an IFH they can request a Tydeman^®^ Tube to use. Consent will be sought retrospectively as per the rest of the trial. This cohort will be in addition to the recruitment target of 30 women for each device. Outcome data will be compared with an historical control group of standard practice (using no device).

Recruited participants and clinicians involved in device use will be asked to complete a questionnaire regarding their views of the device.

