### Population

Main study; women requiring a CS at full cervical dilatation. Substudy; clincian request for a Tydeman Tube for women found to have an IFH at CS between 7 and 9 cm dilatation.

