### Patient recruitment

A full dilatation caesarean section is a common and unpredictable clinical emergency, and there is no consensus of how to predict in which cases an IFH will occur. Around 20% of all deliveries are by emergency caesarean section, and 5–7% of these are performed at full dilatation. In usual clinical practice, use of manoeuvres and/or disimpaction devices would be at the discretion of the operating team. We have designed the recruitment and consent process as per the protocols of similar established emergency obstetric trials (for example the COPE trial) [19].

LIFT participants will be recruited via the following emergency pathway, see Fig. 2.

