### Outcome measures

#### Primary outcome

Time from uterine incision to delivery of baby (seconds).

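### The non-inferiority objective concerns impacted fetal heads, but the primary comparison covers all full-dilatation caesareans, so its verdict would not establish non-inferiority in impacted cases

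*Protocol article*

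**What the plan says.** **Objective.** Under Aims and objectives, the effectiveness of the Tydeman Tube is to be judged against that of the Fetal Pillow, with the purpose worded "for managing an IFH at full dilatation CS, by comparing time from uterine incision to delivery after using the devices". The overall aim, in the same section, is also framed as management of an IFH.

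**Population.** The Population section gives "Main study; women requiring a CS at full cervical dilatation". The inclusion criteria for the main study contain no IFH requirement. Those for the 7–9 cm substudy do, so the protocol draws the distinction elsewhere.

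**Frequency of IFH.** The Background puts it at "16–32% of all those a full dilatation". Patient recruitment adds that "there is no consensus of how to predict in which cases an IFH will occur".

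**Device use.** Under Design, the Pillow is "inserted and inflated prior to full dilatation CS, in all eligible women". The Tube is inserted before all full-dilatation caesareans and "will be used to elevate the fetal head if felt to be required during the caesarean by the operating surgeon".

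**Outcome and margin.** The primary outcome is "Time from uterine incision to delivery of baby (seconds", with no restriction to IFH. The sample-size section sets the margin at a 97 s increase in the mean, with 30 women per arm (up to 40) and a one-sided alpha of 0.05. Impaction is recorded only as a clinician's perception, among the secondary outcomes.

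**The concern.** The claim and the comparison refer to different groups of women. If most women in each arm have no impaction, a device difference confined to impacted cases is averaged over many women in whom it does not occur. In a superiority trial that dilution would work against the hypothesis; in a non-inferiority trial it works in its favour. The trial could meet its criterion, and its objective as worded would then read as an answer about managing an IFH, while a sizeable disadvantage in those cases went undetected.

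The margin's rationale points the same way. It rests on average delivery time going beyond 3 minutes and the association of such times with hypoxic ischaemic encephalopathy. If long deliveries are concentrated in impacted cases, a mean over all women is a weak guide to them.

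**Working it through.** **Inputs from the protocol.** Mean 97 s, SD 94 s, margin 97 s, n = 30 per arm, one-sided alpha 0.05 (Data analysis, sample size and power calculations). IFH share p = 0.16 to 0.32 (Background).

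**Inputs assumed.** (a) The devices differ only in IFH cases. (b) The SD of 94 s applies throughout; the protocol gives no IFH-specific mean or SD. (c) For the simulation, times are lognormal with mean 97 s and SD 94 s.

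**The plan's own figure.** SE = 94 × √(2/30) = 24.27 s. Power at a true difference of zero = Φ(97/24.27 − 1.645) = 99.1%, against the stated 95%. On the stated inputs 21 per arm would give 95%. This separate discrepancy leaves the sample larger than needed for the all-comer test and does not affect the present point.

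**Expected IFH cases per arm.** 30 × 0.16 = 4.8; 30 × 0.32 = 9.6.

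**Dilution.** Under (a), overall difference = p × d, where d is the extra Tube time in IFH cases.

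- For the overall difference to equal the margin, d = 97/0.32 = 303 s to 97/0.16 = 606 s.
- If d = 97 s, the overall difference is 0.16 × 97 = 15.5 s to 0.32 × 97 = 31.0 s.

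**Probability of declaring non-inferiority.** The normal approximation is Φ((97 − p·d)/SE − 1.645). At d = 97 s:

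- p = 0.16: Φ((97 − 15.5)/24.27 − 1.645) = 96%
- p = 0.32: Φ((97 − 31.0)/24.27 − 1.645) = 86%

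A lognormal simulation with a Welch interval gives lower figures, because the times are skewed:

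| Scenario (n = 30 per arm) | IFH 16% | IFH 32% |
|---|---|---|
| Tube 97 s slower in IFH only | 93% | 83% |
| Tube 180 s slower in IFH only | 80% | 42% |
| Tube 97 s slower in IFH and 40 s slower in all others | 67% | 52% |
| Tube 97 s slower in IFH only, margin halved to 48.5 s | 42% | 19% |

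Simulated values vary by about one percentage point between runs. For comparison, a test aimed at IFH cases would pass at nominally 5% when the true delay in those cases equals the margin.

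Row 3 relaxes assumption (a). Row 4 keeps (a) and changes only the margin, which shows how much of the effect the margin contributes.

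**Could the planned sample support the IFH claim directly?** With the same margin and SD applied to 4.8 to 9.6 IFH cases per arm, power would be about 48% to 73%. Reaching 21 IFH cases per arm would take 21/0.32 = 66 to 21/0.16 = 132 full-dilatation caesareans per arm. The claim therefore cannot be moved onto the impacted subset at the planned size.

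**The case against.** **All-comer enrolment is justified.** The protocol says there is no agreed way to predict IFH, and the Pillow goes in before the operation. IFH judged at surgery is observed after the device has acted and may have been prevented or masked by it. A primary analysis restricted to such cases would be biased. This stands: the point concerns the claim, not the population.

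**The size rests on assumptions.** The Pillow is inflated in every eligible woman and could change delivery times where there is no impaction. A reader might infer that the arms must look alike in those women; the documents do not say so, and row 3 of the table shows that the pass rate depends on it. The 16–32% is a cited general estimate, not this unit's rate, and the protocol does not state which caesareans produced the 97 s and 94 s. This stands, and the figures are illustrations under stated assumptions.

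**The margin does much of the work.** Row 4 confirms this. Dilution alone does not account for the high pass rates.

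**Two stronger readings are tempting.** The first is that Tube elevation always falls inside the timed interval. The Design section places it during the caesarean, whereas the clock starts at uterine incision, and the order of the two is not stated. The second is that a Tube that is inserted but not pushed has not been used. The Background describes its wide bore as also letting air in to relieve a vacuum, so insertion may itself have an effect. Neither reading is needed here.

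**The protocol states an objective, not a conclusion, and supportive summaries are ordinary SAP content.** Their absence is no finding. But an SAP that analyses the stated outcome in the stated population would not repair an objective that names a different target.

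**Conclusion.** The mismatch holds on the protocol's text: the non-inferiority objective names IFH, while the outcome, margin and sample apply to all eligible full-dilatation caesareans, of which an estimated 68–84% have no impaction. The trial can support a statement about two routine device policies. It cannot, as designed, support one about effectiveness in impacted cases.

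A delay equal to the whole margin in every IFH case would be declared non-inferior about 93% to 83% of the time, if device differences arise only in IFH cases and times are lognormal with the planning mean and SD. This falls to about 67–52% with a further 40 s delay in other women, and part of it is due to the wide margin. The direction is firmer than the size. With no IFH-specific mean or SD in the protocol, how harmful a given delay would be in impacted cases cannot be judged from it.

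**What to change.** 1. Restate the primary objective and the permitted conclusion as non-inferiority of two routine policies in all eligible full-dilatation caesareans: Pillow inflated in all before surgery, and Tube inserted in all with elevation if the surgeon judges it needed.
2. Remove the reference to managing an IFH from the non-inferiority claim.
3. State that the all-comer result does not establish non-inferiority in impacted cases.
4. If incision-to-delivery time is summarised in women with clinician-perceived IFH, label it descriptive, with no non-inferiority verdict, because that perception is formed after the device has been placed.

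Population, device use, primary outcome and sample size stay as they are. The changes are to wording only, and the questionnaire already collects perceived impaction. The cost is a narrower headline claim.

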### Design

This is a prospective non-inferiority observational comparison trial with two sequential interventional arms, the first using the Fetal Pillow^®^ and the second using the Tydeman^®^ Tube. Each device has regulatory approval for routine use and therefore can be introduced into clinical practice.

At trial commencement, obstetric and midwifery staff will be trained to use the Fetal Pillow^®^ by members of the research team during dedicated training sessions. The Fetal Pillow^®^ will then be introduced into clinical practice for 3–6 months for use during all full dilatation CS, or until the recruitment target is reached (*n* = 30). The Fetal Pillow^®^ will be inserted and inflated prior to full dilatation CS, in all eligible women. Consent will be sought retrospectively, see ‘Patient Recruitment’. Once the recruitment target for the Fetal Pillow^®^ has been reached, the device will be withdrawn from clinical areas and will no longer be available for use.

Obstetric and midwifery staff will then be trained to use the Tydeman^®^ Tube and the above process repeated over a 3–6-month period, or until the recruitment target is reached (*n* = 30). For eligible women, the Tydeman^®^ Tube will be inserted prior to commencement of all full dilatation CS and will be used to elevate the fetal head if felt to be required during the caesarean by the operating surgeon.

Should recruitment be reached in a shorter time frame than expected then each arm will continue for the set time frame (3–6 months) to allow for increased data collection and loss to follow up, to a maximum of 40 women per arm.

During the Tydeman^®^ Tube arm of the study, additional Tydeman^®^ Tubes will be available for clinicians to use at their discretion for caesarean sections performed at 7–9 cm cervical dilatation as per the manufacturer’s Instructions for use, which stipulates that the Tydeman^®^ Tube can be used from 7 to 10 cm. If, during a caesarean section, the operating surgeon unexpectedly encounters an IFH they can request a Tydeman^®^ Tube to use. Consent will be sought retrospectively as per the rest of the trial. This cohort will be in addition to the recruitment target of 30 women for each device. Outcome data will be compared with an historical control group of standard practice (using no device).

Recruited participants and clinicians involved in device use will be asked to complete a questionnaire regarding their views of the device.

### Setting

The LIFT trial will be conducted at St Thomas’ Hospital, a tertiary level maternity unit in South London, UK. Neither device is currently in use at this site.

### Population

Main study; women requiring a CS at full cervical dilatation. Substudy; clincian request for a Tydeman Tube for women found to have an IFH at CS between 7 and 9 cm dilatation.

### Inclusion and exclusion criteria

#### Inclusion criteria

For main study:

Women undergoing full dilatation caesarean sectionSingleton pregnanciesCephalic presentationAged > 16 years old≥ 37 weeks’ gestation

For sub-study:

Women undergoing caesarean section at 7–9 cm where IFH is encounteredSingleton pregnanciesCephalic presentationAged > 16 years old≥ 37 weeks’ gestation

For clinician sub-cohort:

Operating surgeon/surgeons or operator of deviceWilling to complete questionnaire

#### Exclusion criteria

For main study:

Allergy to silicone rubberMajor congenital abnormalitiesMajor anomaly of the fetal head (i.e. large encephalocele)Intrauterine deathSuspected chorioamnionitisActive genital infection inc. Herpes Simplex Virus

For sub-study:

Allergy to silicone rubberMajor congenital abnormalitiesMajor anomaly of the fetal head (i.e. large encephalocele)Intrauterine deathSuspected chorioamnionitisActive genital infection inc. Herpes Simplex Virus

For clinician sub-cohort:

Clinician not directly involved in use of device or operation

### Trial flowchart

Figure 1 shows the trial flowchart outlining the study pathway.

**Fig. 1 Fig1:**
[figure not shown]
Trial flowchart

### Patient recruitment

A full dilatation caesarean section is a common and unpredictable clinical emergency, and there is no consensus of how to predict in which cases an IFH will occur. Around 20% of all deliveries are by emergency caesarean section, and 5–7% of these are performed at full dilatation. In usual clinical practice, use of manoeuvres and/or disimpaction devices would be at the discretion of the operating team. We have designed the recruitment and consent process as per the protocols of similar established emergency obstetric trials (for example the COPE trial) [19].

LIFT participants will be recruited via the following emergency pathway, see Fig. 2.

**Fig. 2 Fig2:**
[figure not shown]
LIFT recruitment via emergency pathway

Use of the Tydeman Tube or Fetal Pillow during full dilatation caesarean section will occur if eligibility criteria is met at time of consent for caesarean section. Postnatally, once the woman is stable and ideally within 24 hours (but potentially up to 72 hours, or prior to transfer to another hospital/discharge), full study information will be provided to the woman. Before approaching participants, the research team will ensure this is appropriate timing with a member of the clinical team. A patient information leaflet will be provided and if the patient is willing to participate, permission will be sought for disclosure of identifiable data, and the woman will be asked to sign the trial consent form.

Should a participant not regain capacity to consent within 72 hours, full study information should be provided as soon as possible to her Personal Consultee or Nominated Consultee (should a Personal Consultee not be available). The Personal or Nominated Consultee will be asked to sign the Personal or Nominated Consultee Declaration Form. Should a woman regain capacity to consent after this time and before 4 weeks postnatally, then full study information will be provided to them, and written informed consent will be sought should they wish to participate in the study.

Consent is expected to be sought for all women prior to discharge or transfer, however if this is not enacted, postal or electronic consent should be sought no more than 4 weeks after the event. Women should be contacted by trial staff within 5 working days to inform them of their involvement and provide details of the trial. If the woman is not willing to provide consent, her details will be withdrawn. If the woman is willing to provide consent, a patient information leaflet and consent or electronic consent form will be sent via post or email to the address provided by the woman, depending on their preference.

Participation in the study is voluntary and participants are able to withdraw their consent at any time. This option will be provided within the written information on the participant information sheet and discussed at the time of informed consent. The participant will be told that withdrawal at any time would not affect their clinical care. If consent is withdrawn then any outcome data collected will not be used for analysis and the participant will be removed from the study. If consent for data storage and analysis is withdrawn at any time the participants data will be withdrawn from the analysis.

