### Data analysis, sample size and power calculations

Time between uterine incision and delivery of the baby reflects the degree of difficulty in disimpacting the fetal head and will be used as the primary outcome measure to compare efficacy of the devices. Estimation of usual time from uterine incision to delivery was obtained from a robust clinical database capturing all maternity statistics from our unit over a period of one year. Sample size calculation was based on an observed mean time from uterine incision to delivery of 97 s (standard deviation 94 s).

To demonstrate that the Tydeman^®^ Tube is non-inferior to the Fetal Pillow^®^, non-inferiority was defined as an increase in uterine incision to delivery time of no more than 97 s (corresponding to a doubling of mean time to 194 s). We chose doubling of the time from uterine incision to delivery as a clinically important outcome, as this would take the average time to over 3 min. A delivery time of over 3 min at caesarean section has been associated with the development of hypoxic ischaemic encephalopathy, hence exceeding this is non-desirable.

30 participants per arm provides 95% power (one-sided alpha 0.05) to determine non-inferiority. We therefore aim to recruit 30 participants to each arm as minimum. If the recruitment target is reached sooner than expected (i.e. within 3 months) then recruitment will continue up to 40 participants per arm for a maximum of 6 months. In the substudy the Tydeman^®^ Tube will only be used when an IFH is encountered unexpectedly. We do not have data to support how frequently this may occur during the study period and this will be an observational arm without pre-defined sample size.

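### Any withdrawal of consent removes outcome data already collected, although the primary outcome is complete at delivery; this avoidable exclusion can depend on the outcome

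*Protocol article*

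**What the plan says.** All three rules stand in the Patient recruitment section of the protocol article.

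- **Refusal of initial consent:** "If the woman is not willing to provide consent, her details will be withdrawn".
- **Withdrawal after consent, for any reason:** "If consent is withdrawn then any outcome data collected will not be used for analysis and the participant will be removed from the study".
- **Withdrawal of consent to data use:** "If consent for data storage and analysis is withdrawn at any time the participants data will be withdrawn from the analysis".

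The same section places information and consent after the birth: ideally within 24 hours, up to 72 hours, and by post or electronically up to 4 weeks. The primary outcome is the time from uterine incision to delivery, so it is complete before any of these decisions. The Design section describes a "prospective non-inferiority observational comparison trial with two sequential interventional arms", with a target of 30 women per arm and a ceiling of 40.

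**The concern.** The second and third rules deal with different requests. One is to stop taking part; the other is to stop the use of one's data. Both lead to exclusion from the analysis, so the third rule adds nothing to the second. A woman who wants only to skip the questionnaire or further contact loses a measurement that was already valid and complete.

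Her choice is made with knowledge of the birth. If women with a slow or traumatic delivery withdraw at a different rate, the analysed set is selected on the outcome. The arms are not randomised and are recruited in different periods, so withdrawal behaviour may also differ between devices. With about 30 women per arm, one to three exclusions can move a mean. Recruiting up to 40 can restore the numbers but not undo the selection. What is at stake is the primary difference and the comparative maternal and neonatal outcomes.

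**Working it through.** **Inputs** (Data analysis, sample size and power calculations): "observed mean time from uterine incision to delivery of 97 s (standard deviation 94 s"); margin "an increase in uterine incision to delivery time of no more than 97 s"; "30 participants per arm provides 95% power (one-sided alpha 0.05) to determine non-inferiority". The 180 s cut-off in step 3 comes from the 3-minute figure in the same section ("A delivery time of over 3 min at caesarean section has been associated with the development of hypoxic ischaemic encephalopathy"). Assumed, because the article gives neither: the lognormal shape and every exclusion rate.

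**1. The plan's own figure, and whether lost numbers matter.** SE = 94 × √(2/30) = 24.27 s; 97/24.27 = 3.997; power = Φ(3.997 − 1.645) = 99.1%. The stated 95% is not reproduced: it needs 2 × (1.645 + 1.645)² × (94/97)² = 20.3, so 21 per arm. The stated power is thus conservative, which is a separate matter. With 27 or 24 women per arm, power is still 98.4% or 97.3%. The issue is bias, not power.

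**2. Upper bound: the slowest women lost from one arm only.** σ² = ln(1 + (94/97)²) = 0.662, so σ = 0.814. The mean of times below quantile p is 97 × Φ(z_p − σ)/p.

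- Slowest 10% lost: 97 × Φ(1.282 − 0.814)/0.9 = 97 × 0.680/0.9 = 73.3 s, which is 23.7 s lower.
- Slowest 1 in 30 lost: 97 × Φ(1.834 − 0.814)/0.9667 = 97 × 0.846/0.9667 = 84.9 s, which is 12.1 s lower.
- Simulating samples of exactly 30 and dropping the slowest 3 or 1 gives 74.8 s and 86.5 s, which are 22.2 s and 10.5 s lower.

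The shift is therefore about 22–24 s (23–24% of the margin) or 10–12 s (11–12%).

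**3. The same behaviour in both arms, with the Tube truly 97 s slower.** Simulation with 30 analysed women per arm; 5% of women with times up to 180 s are excluded, and a higher share above 180 s. The exclusions here pool refusal and withdrawal.

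| Excluded above 180 s | Expected difference, Tube adds 97 s | False non-inferiority | Expected difference, Tube doubles every time | False non-inferiority |
|---|---|---|---|---|
| No exclusions at all | 97 s | 4.6% | 97 s | 9.4% |
| 20% | 95.7 s | 5.8% | 90.6 s | 12.8% |
| 30% | 94.4 s | 6.4% | 85.6 s | 17.1% |
| 50% | 91.0 s | 10.5% | 73.6 s | 30.0% |

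With 10,000 simulated trials per cell, the percentages carry an error of about ±0.4 points near 5% and ±0.9 points near 30%. The 9.4% start comes from skewness and unequal variances, not from consent. Excluding 10% regardless of outcome leaves the expected difference at 97 s.

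**4. Direction.** If the arms are truly equal and behaviour is the same, the bias in the difference cancels. If the Tube is slower and behaviour is the same, the difference shrinks, as in step 3. If slow cases are lost mainly from the Tube arm, the bias favours non-inferiority; if mainly from the Fetal Pillow arm, it works against it.

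**The case against.** The strongest reply is that most of the mechanism is legitimate. Deferred consent follows from an unpredictable emergency, and not using the data of a woman who refuses is ordinary practice. Rewording the withdrawal rule recovers none of the refusals. It helps only women who sign and later withdraw, who may be few, since follow-up runs to at most 4 weeks. The article gives no rate. All of this stands, and it limits the point to withdrawal after consent.

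One can also argue that, once the device has been used, data use is nearly all that study participation consists of, so the two kinds of withdrawal are the same. That does not fully hold: the questionnaire, further contact and further data collection remain, and the protocol itself gives consent for data storage and analysis its own sentence.

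The figures are open to challenge too. Step 2 assumes perfect selection in one arm and none in the other; step 3 includes refusals. Neither estimates the effect of the withdrawal rule alone. They show only how sensitive a comparison of this size is.

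A reader might infer that the rule hides serious adverse events. The documents do not support that. Under Reporting responsibilities, serious events are monitored and reported from the time of the procedure, with no consent condition stated, and under Assessment of safety a data monitoring committee reviews the reports. The text speaks of data not being analysed and of removal from the study, not of erasing reports. What remains is that the article does not say whether reports already made are kept after removal.

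**Conclusion.** The point holds as a defect in a stated rule. Outcome data that are complete and validly collected leave the analysis on any withdrawal, and this exclusion can depend on the outcome. It is avoidable, because the protocol already has a separate provision for withdrawal of consent to data use.

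The size is not known. For one or three women lost from one arm of 30, the shift in that arm's mean is at most about 10–12 s or 22–24 s, given lognormal times with the protocol's mean and SD; weaker selection gives less.

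Three stronger readings go beyond the documents. They permit outcome-dependent withdrawal but do not show that it will happen. The bias does not always favour non-inferiority; that needs a truly slower Tube with similar behaviour in both arms, or heavier loss of slow cases from the Tube arm. And counts of women who declined or withdrew by arm, or a sensitivity analysis for them, may be in the full protocol or the SAP, so their absence from the article is not a fault.

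**What to change.** Reword the withdrawal paragraph in Patient recruitment, and the matching text in the information sheet and consent form, along these lines:

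- Withdrawal from participation stops further contact and data collection; data collected up to that point stay in the analysis.
- Data are removed only when consent for data storage and analysis is itself withdrawn.
- Serious adverse event reports already made from the time of the procedure are kept in de-identified form for the data monitoring committee.

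Women who refuse initial consent remain excluded, so selection through refusal is not cured.

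The cost is a wording amendment with ethics agreement to the change; no additional data collection is needed. The Trial status section gives March 2026 as the planned start of recruitment. The change is cheapest before or early in recruitment, since data once excluded may not be recoverable.
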